### Participants

Eligible participants are (1) female patients (2) aged 18 years or older with (3) newly diagnosed breast cancer who are scheduled to undergo therapeutic breast surgery at Robert-Bosch Hospital following initial diagnosis—written informed consent is required prior to study participation (4).

Patients will be excluded if (1) they have been diagnosed with an anxiety disorder within the previous 12 months or (2) if, in the opinion of the principal investigator, a psychological or mental condition precludes safe or appropriate participation in the study. Including participants with a diagnosed anxiety disorder may have introduced substantial variability in anxiety response due to underlying psychopathology and/or ongoing treatment. As such, this could act as a confounding factor, influencing preoperative anxiety beyond the transient, situational anxiety associated with surgery and limiting the internal validity of our study. Additional exclusion criteria include (3) the use of hearing aids; (4) the presence of skin irritation, inflammation, or eczema of the ear; (5) pregnancy; (6) insufficient proficiency in the German language; (7) unwillingness to permit storage and processing of personal health data as required by the study protocol; (8) missing or incomplete informed consent; and (9) prior acupuncture treatment (including NADA auricular acupuncture or acupressure) within the previous 3 months. According to the German S3 guideline on breast cancer [29] and the AGO Breast Committee recommendations for early breast [30], therapeutic surgery is typically scheduled within 3 to 6 weeks after histological confirmation of the diagnosis or 3 to 6 weeks after completion of neoadjuvant systemic therapy when indicated. Patients are usually admitted on the day before or the morning of surgery. Perioperative care is delivered in accordance with institutional protocols, including preoperative assessment by the anesthesia team, general anesthesia, multimodal analgesia, and risk-adapted PONV prophylaxis. The typical length of hospital stay is 1 to 3 days for breast-conserving surgery and 3 to 5 days for mastectomy, with or without reconstruction. All patients enrolled in the study receive this standard care regardless of group allocation.

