**Figure 1. F1:**
[figure not shown]
SPIRIT (Standard Protocol Items: Recommendations for Interventional Trials) 2025 participant timeline: schedule of enrollment, interventions, and assessments. NADA: The National Acupuncture Detoxification Association.

The primary outcome of this study is preoperative state anxiety prior to surgery (T1) measured using the State subscale of STAI-S [33].

Secondary outcomes include postoperative anxiety, preoperative and postoperative pain, PONV, use of analgesic and antiemetic medication, postoperative complications, specific surgery-related preoperative anxiety, trait anxiety, depressive symptoms, and therapy decisions at follow-up.

Postoperative anxiety will be measured using STAI-S after transfer to the surgical ward (T2) and daily during hospitalization (T3-Tx). Current pain intensity will be assessed using a Numerical Rating Scale (NRS; 0‐10) where higher scores represent higher pain intensity and will be measured both pre- (T0 and T1) and postoperative (T2-Tx). PONV will be assessed jointly using an NRS (0‐10) where higher scores represent higher symptom severity. Assessments will be performed after transfer to the surgical ward (T2) and daily during hospitalization (T3-Tx). This approach is consistent with current perioperative research and clinical practice, as nausea and vomiting are considered to share common risk factors and are addressed together in current clinical guidelines for the prevention and management of PONV [40,41]. For outcomes assessed daily during hospitalization, the same standardized questions were used at each assessment timepoint to ensure consistency across repeated measurements.

Analgesic consumption and the use of antiemetic medication will be extracted from medical records and summarized from surgery until discharge. Due to possible variability in prescribed agents and dose adjustments based on symptom severity, medication use will be summarized by drug class (eg, opioids, nonopioid analgesics, and antiemetics). Opioid consumption will be converted to oral morphine equivalents (OME) to allow standardized comparisons across participants [42]. Nonopioid analgesics and antiemetics will be summarized as cumulative dose within class and frequency of administration (eg, number of doses given).

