### Data Analysis

Preoperative outcomes assessed at T1 (preoperative state anxiety and preoperative pain) will be analyzed using ANCOVA with the treatment group as the between-subject factor (NADA vs CTRL) and the respective baseline value as the covariate. Adjusted mean differences between groups and effect sizes (Cohen *d*) will be reported with corresponding 95% CIs. A 2-sided significance level of 5% will be applied.

In an exploratory analysis, the time interval between the T1 STAI-S assessment and surgery will be included as an additional covariate to account for potential variability in the timing of the anxiety assessment. Some variation in timing is expected due to the practical constraints of conducting the study in a clinical setting, and preoperative anxiety may increase as surgery approaches.

Repeated continuous postoperative outcomes T2-Tx (state anxiety, pain, PONV) will be analyzed using linear mixed-effects models including fixed effects for treatment group, time, and the group × time interaction, with participants included as a random effect.

Cumulative analgesic and antiemetic medication use from surgery to discharge will be compared between groups using linear regression models. If substantial violations of model assumptions are observed that cannot be addressed through appropriate data transformations, alternative analyses will be used, such as generalized linear models. Overall postoperative complication rates will be analyzed using logistic regression models and reported as odds ratios (ORs) with corresponding CIs.

Exploratory moderation analyses will be performed to evaluate whether baseline characteristics, including surgery-specific preoperative anxiety, trait anxiety, and depressive symptoms, modify the treatment effect on the primary outcome. Separate models will be fitted for each moderator as extensions of the primary ANCOVA model. Each model will include the baseline covariate, the treatment group, the respective moderator, and the group x moderator interaction term. A significant interaction term will be interpreted as evidence of a moderating effect.

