Several limitations must also be considered. Due to the nature of the intervention, blinding of participants and treating personnel is not feasible. This might introduce bias in the measurement of outcomes, particularly in the assessment of patient-reported outcomes such as anxiety and pain. To address this limitation, objective secondary outcomes, including medication use and postoperative complications, are assessed to provide clinically relevant endpoints less susceptible to reporting bias. Furthermore, the study does not include a sham control condition. The primary aim was to evaluate the efficacy of NADA auricular acupressure as an adjunct to routine care rather than to isolate specific acupoint-related effects. Consequently, the design does not allow differentiation between specific physiological effects of point stimulation and nonspecific effects related to expectation, therapeutic attention, or contextual influences. In addition, the sample size estimation was based on detecting a minimal clinically important difference in preoperative state anxiety as measured by the STAI-S. The study is therefore adequately powered for the primary endpoint but is not specifically powered to detect statistically significant differences in secondary outcomes. These should be considered exploratory, and effect estimates and corresponding CIs will be reported to facilitate interpretation of the magnitude and precision of observed differences.

Despite these limitations, the study addresses an important gap in the field of integrative oncology. There is growing interest among patients and health care providers in nonpharmacological strategies to improve perioperative well-being. However, integration of such approaches into clinical practice requires evidence from rigorously designed randomized trials. If NADA auricular acupressure proves effective in reducing perioperative anxiety and pain, it could represent a low-risk, low-cost, and easy-to-implement adjunct to standard care. Conversely, if no significant benefit is observed, the study will still provide important evidence to reconsider current assumptions regarding the role of auricular acupressure in perioperative oncology. Additionally, it will provide valuable information regarding effect sizes and variability in this patient population, thereby informing the planning of following studies.

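### Medication use is compared as a surgery-to-discharge total with no surgery-type term, so it mixes daily need with length of stay; nonopioid and antiemetic doses are also summed raw across agents

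*Protocol article*

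**What the plan says.** Outcomes sets the window: "Analgesic consumption and the use of antiemetic medication will be extracted from medical records and summarized from surgery until discharge". Data Analysis sets the model: "Cumulative analgesic and antiemetic medication use from surgery to discharge will be compared between groups using linear regression models". Generalized linear models are the fallback, but only if model assumptions fail badly. Neither section names a surgery-type term, a fixed window or a rate for these totals.

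Participants gives the expected stay: "The typical length of hospital stay is 1 to 3 days for breast-conserving surgery and 3 to 5 days for mastectomy". Randomization and Blinding stratifies allocation by those same two types of surgery.

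On combining drugs, Outcomes expects prescribed agents to vary. For opioids it says: "Opioid consumption will be converted to oral morphine equivalents (OME) to allow standardized comparisons across participants". For the other classes it says: "Nonopioid analgesics and antiemetics will be summarized as cumulative dose within class and frequency of administration". Standard care includes "general anesthesia, multimodal analgesia, and risk-adapted PONV prophylaxis".

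On the role of these data, the Discussion answers the lack of blinding by noting that "objective secondary outcomes, including medication use and postoperative complications, are assessed to provide clinically relevant endpoints less susceptible to reporting bias". Data Analysis and the Discussion both class secondary outcomes as exploratory.

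**The concern.** A total that runs to discharge has a different observation window for each patient. On the stated stays, the window can differ fivefold (1 to 5 days). Three consequences follow.

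- **Precision.** Much of the spread in the total reflects days observed. Part of that spread is predictable from the stratum, which the model leaves out.
- **Interpretation.** Discharge happens after randomization, and patients and staff know the allocation. If one arm goes home earlier, its total falls even when daily need is unchanged.
- **Units.** Raw doses of different nonopioids or antiemetics have no common scale, so the choice of agent enters the sum.

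At stake is the one group of outcomes, with complications, that the article offers as less open to reporting bias than self-reported anxiety and pain. The primary outcome is not affected.

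**Working it through.** **The plan's own figure.** The article gives no variance or power for medication use. Its sample size concerns the primary outcome and reproduces: ANCOVA with f = 0.4, one covariate and two-sided 5% gives power 0.799 at N = 51 and 0.807 at N = 52. Dropout inflation gives 52/0.80 = 65, and 66 makes the arms equal. I use N = 66 below.

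**Spread from length of stay.** From the article: stays of 1–3 and 3–5 days. Assumed: 35% mastectomy, with whole days equally likely within each range.
- Mean = 0.65 × 2 + 0.35 × 4 = 2.7 days.
- Variance = 2/3 (within stratum) + 0.35 × 0.65 × 2² = 0.667 + 0.910 = 1.577, so SD = 1.26 and CV = 1.26/2.7 = 46.5%.
- Share of the variance due to the stratum = 0.910/1.577 = 58%.

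**How much of the total is stay and how much is need.** Total = daily need × days. With constant daily use, 20–50% mastectomy and a between-patient CV of daily need from 0.8 down to 0.3, stay explains about 20–67% of the variance of the total and daily need 27–68%. If use halves each day (CV 0.5, 30% mastectomy), stay explains about 13% and need 81%.

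**Power for a true 30% reduction in daily need.** Simulation with N = 66, 35% mastectomy, CV of daily need 0.6 and equal stays in both arms. All inputs except N and the stay ranges are assumed. Ranges cover repeated runs.

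| Daily use | Total | Total + stratum | First-day window |
|---|---|---|---|
| Constant, no day-to-day variation | 41–43% | 50–51% | 66–67% |
| Halves daily, no day-to-day variation | 60–61% | 62–63% | 67% |
| Constant, within-patient daily CV 0.5 | 35–36% | 43% | 41% |
| Halves daily, within-patient daily CV 0.5 | 47–49% | 48–50% | 42% |

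The stratum term helps in every row, by about 1 to 10 points. The first-day window helps only when use hardly varies from day to day within a patient.

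**Error rate with no true difference and equal stays.** If allocation is simulated without stratification, the total rejects 4.8% of the time. With allocation stratified by surgery type, as planned, and constant use, the model without the stratum rejects about 2.2%. Its standard error still carries between-stratum variation that the design has removed from the group contrast. The shortfall is smaller if use falls quickly after surgery.

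**Error rate when discharge timing differs.** No difference in daily need, but half of the intervention patients with stays over 1 day leave one day earlier.
- The mean shift is 0.5 × (1 − 0.65/3) = 0.39 day. With constant use the total falls by 0.39/2.7 = 14.5%; if use halves daily it falls by 6.8%.
- The total shows a significant difference in about 10–14% of trials with constant use, and 6–8% if use halves daily.
- The stratum term does not cure this (about 17% in the run that gave 14% without it). A fixed window stays near 5%.
- A per-day rate is sound with constant use (4–5%) but rejects about 9% if use halves daily.

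**Raw dose sums.** Assume two agents, each given to half the patients, whose dose per administration differs r-fold.

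| r | Variance of summed dose explained by number of doses | Explained by agent |
|---|---|---|
| 2 | 64% | 29% |
| 5 | 31% | 55% |
| 15 | 21% | 63% |

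The article names no agents, so r is unknown.

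**The case against.** The strongest reply is that total in-hospital consumption is a legitimate pragmatic quantity and that stratified randomization balances the only driver of stay the article names. That stands: with equal stays the test does not reject too often, and the cost is precision. A spurious drug-sparing effect requires the arms to differ in discharge timing. The article gives no evidence that they will, only the conditions under which they could.

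It can also be said that Data Analysis promises to account for variation in hospital days. That sentence concerns longitudinal data and leads into rules on which missing daily observations are imputed. It supplies no method for a single cumulative total.

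On units, opioids are standardized, and the number of doses is already listed for the other classes: "Nonopioid analgesics and antiemetics will be summarized as cumulative dose within class and frequency of administration (eg, number of doses given"). What remains is that the raw sum is kept and that Data Analysis does not say which of the two measures is compared.

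A reader might infer that the outcome measures days in hospital and drug choice rather than need. The documents do not support that, because need remains a substantial part of the total in every scenario above. A reader might also infer that a 24-hour window should replace the total, citing the 66–67% power. That figure assumes almost no day-to-day variation; with it, the window has 41–42% power against 43–50% for the stratum-adjusted total. Finally, the article does not say that prophylactic antiemetics are counted. Starting the window at surgery only makes it possible.

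An analysis plan not shown here may add detail, but the article itself already fixes the window and the model.

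**Conclusion.** The point holds in a limited form and is worth correcting. The medication total mixes daily need with length of stay, and the stated model omits the stratum that predicts stay. With similar stays in both arms, this costs about 1 to 10 points of power for an assumed 30% reduction and makes the error bars too wide. With a discharge difference of the assumed kind, the false-positive rate for daily need rises to about 6–14% on the unadjusted total. Raw dose sums for nonopioids and antiemetics add variation from choice of agent, to an extent the article does not allow one to fix.

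These sizes rest on assumed mastectomy share, variation in need, decline of use and day-to-day variation, and should be read as ranges. The primary outcome and the sample size are untouched. The outcomes are exploratory, so this is an improvement to make, not a threat to the trial's main conclusion. It matters because the Discussion uses medication use to offset unblinded self-report.

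**What to change.** 1. Add the surgery-type stratum to the medication regression models.
2. For nonopioids and antiemetics, name number of administrations (or a stated dose-standardized unit) as the compared measure, in place of raw dose summed within class. Keep morphine equivalents for opioids.
3. Report length of stay by arm next to the totals. Do not adjust for it as a covariate, because it is determined after randomization.
4. Add a fixed common-window analysis, for example the first 24 hours after surgery, as a sensitivity analysis beside the total and not in its place.
5. Tabulate prophylactic and later antiemetic doses separately where the records allow.
6. If a power gain is quoted, show it as a range over assumed decline and day-to-day variation in use.

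Items 1 to 3 need no new data. Items 4 and 5 need administration times, and where recorded the indication, from the medical records already being extracted. With 8 of 66 participants recruited at submission, this can be specified now at little cost.

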### Intervention Discontinuation and Adherence

The intervention will be discontinued in the event of adverse reactions, participant requests, or if continuation is deemed inappropriate by the investigator for medical or safety reasons. Participants may withdraw from the study at any time without providing a reason and without consequences for their medical care.

To promote adherence, participants in the intervention group will receive verbal and written instructions detailing instructions regarding acupressure point stimulation and behavioral recommendations during the intervention period. In addition, participants will receive daily visits from study personnel during their hospital stay to reinforce instructions, address questions, and monitor proper application of the auricular patches and safety.

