All analyses will be conducted according to the intention-to-treat (ITT) principle. All randomized participants will be included in the analysis and analyzed according to their allocated group, irrespective of adherence to the intervention. Missing data will be handled using multiple imputation by chained equations (MICE) under the assumption that data are missing at random using the “mice” package for R [46]. Due to the nature of longitudinal data collection, between-participant variation in number of hospitalization days is expected and will be accounted for. Observations expected during hospitalization but not available will be imputed; however, measurements not collected because of hospital discharge will not be imputed. Analyses will be performed on multiply imputed datasets, and parameter estimates across the imputed datasets will be combined using Rubin’s rule.

As a sensitivity analysis, a per-protocol analysis will be conducted, including only participants who adhered to their allocated treatment. Protocol adherence will be defined a priori. Participants in the intervention group will be considered protocol-adherent if they received the ear acupressure prior to surgery and continued the intervention for the subsequent 4 days or until hospital discharge, whichever occurred first. Participants in the control group will be considered adherent if they did not receive ear acupressure before the end of primary data collection (Tx).

In addition, an exploratory exposure-based sensitivity analysis will be performed at 3 months follow-up to assess the association between exposure to ear acupressure and the use of other CIM therapies. To this end, participants will be classified according to actual exposure to ear acupressure, defined as receipt of ear acupressure either during the intervention phase or after discharge in the control group. ORs and corresponding 95% CIs will be calculated to compare the likelihood of using CIM therapies between participants exposed to ear acupressure and those not exposed.

No formal adjustment for multiplicity will be applied, as the trial has a single primary outcome for the confirmatory analysis. Findings for the secondary outcomes, as well as the moderation and sensitivity analyses, are considered subsidiary and exploratory [47].

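### One per-protocol definition serves every outcome, so for the pre-surgery primary outcome (T1) it selects NADA participants on behaviour that falls mostly after T1

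*Protocol article*

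**What the plan says.** The Outcomes section fixes the primary endpoint before the operation: "The primary outcome of this study is preoperative state anxiety prior to surgery (T1) measured using the State subscale of STAI-S". Data Analysis compares it between arms by ANCOVA with the baseline value as covariate, by intention to treat. The same section then adds: "As a sensitivity analysis, a per-protocol analysis will be conducted, including only participants who adhered to their allocated treatment".

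Adherence is said to be defined in advance, and one rule per arm follows. A NADA participant qualifies "if they received the ear acupressure prior to surgery and continued the intervention for the subsequent 4 days or until hospital discharge", whichever comes first. A control qualifies by having had no ear acupressure before Tx, the last in-hospital assessment. No separate rule is given for outcomes measured at T1, and the outcomes to which the per-protocol analysis applies are not listed.

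On stopping, Intervention Discontinuation and Adherence says "The intervention will be discontinued in the event of adverse reactions, participant requests", or on the investigator's judgement. On starting, the Intervention Group section says only that the intervention begins before surgery. The Safety section labels the period from its start to discharge as T1 to Tx.

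**The concern.** Whether a woman keeps the pellets on after T1 cannot change her T1 score. Her T1 anxiety, her tolerance of the pellets or her view of the treatment may well affect whether she keeps them on. Requiring continuation therefore adds nothing to the measurement of exposure at T1; it only selects, and mainly within the NADA arm.

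The receipt condition has a related weakness. It refers to surgery, whereas exposure relevant to the primary outcome must precede the T1 questionnaire.

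What is at stake is the use of the per-protocol result beside the primary result. If it can drop participants who were exposed at T1, and does not guarantee that those kept were exposed, then agreement or disagreement with the intention-to-treat estimate is hard to interpret.

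**Working it through.** **Inputs from the article.** Target difference 8 points and SD 10 (Sample Size Calculation); 66 participants randomised 1:1, so 33 per arm; admission usually the day before or the morning of surgery (Participants); 5 days of wear after application (Intervention Group).

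**Inputs not in the article, assumed.** The fraction *p* of NADA participants who stop early, 10-30%; and the gap *g* in mean T1 score between those excluded and those retained, 3-5 points.

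**The plan's own figure.** ANCOVA F test with f = 0.4, one covariate and denominator df = N - 3: power is 0.799 at N = 51 and 0.807 at N = 52, so 52 is reproduced. 52/(1 - 0.20) = 65, or 66 for equal arms. Nothing below changes this; the 8 points serve as the yardstick.

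**Step 1: when the continuation days fall.** The 4 days can be counted in two ways.
- From surgery: all of them follow T1.
- From application (1 + 4 = the 5 days of wear): if application is the day before surgery, the 4 days are the day of surgery and the next three, and at least those three follow T1. If application is on the morning of surgery, all 4 later days follow T1.

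The second count takes application to be around admission. The daily in-hospital checks and the T1-Tx safety window suggest this but do not state it.

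**Step 2: what the rule does to T1 exposure.**

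| Participant | Exposed at T1 | Status under the rule |
|---|---|---|
| NADA, pellets before T1, stops after surgery while in hospital and within the 4 days | Yes | Excluded |
| NADA, pellets after T1 but before surgery, continues | No | Retained |
| Control, acupressure after T1 but before Tx | No | Excluded |
| Control, none before Tx | No | Retained |

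The first three rows are misclassified for a T1 outcome. The second follows from the wording; no passage plans for it.

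**Step 3: size, raw means.** The whole-arm mean is (1 - p) × retained mean + p × excluded mean. Hence retained mean - whole-arm mean = -p × g, with g = excluded mean - retained mean.
- 0.10 × 3 = 0.3 points (0.3/8 = 3.75% of the target)
- 0.20 × 5 = 1.0 point (12.5%)
- 0.30 × 5 = 1.5 points (18.75%)

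The NADA mean falls if the more anxious stop and rises if the less anxious stop. The definition of the gap matters: measured from the excluded to the whole arm, the shift is p/(1 - p) × gap, giving 0.33, 1.25 and 2.14 points for the same three pairs.

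**Step 4: size, baseline-adjusted.** A large-sample simulation of the ANCOVA was run with true effect 0, SD 10, baseline-T1 correlation 0.5 (assumed), all controls retained, and later NADA adherence depending on the T1 score. Columns are odds ratios for adherence per SD lower anxiety; cells are the per-protocol estimate in points.

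| NADA adherence | OR 1 | OR 1.5 | OR 2 | OR 3 |
|---|---|---|---|---|
| 90% | -0.01 | -0.29 | -0.50 | -0.74 |
| 80% | -0.03 | -0.59 | -0.94 | -1.39 |
| 70% | -0.01 | -0.91 | -1.45 | -2.10 |

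The OR 1 column is simulation noise around 0. The last cell exceeds 1.5 because so steep a dependence implies a gap wider than 5 points. By symmetry, the signs reverse if more anxious women adhere better.

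**The case against.** The best defence is that little hangs on this. Intention to treat is the main analysis, sensitivity analyses are declared exploratory, and no sample size or confirmatory test uses the per-protocol set. That stands and limits the consequence.

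Second, the article does not say that the per-protocol analysis covers the primary outcome, and the continuation clause suits the T2-Tx outcomes. A SAP, not shown here, might hold outcome-specific sets. The clause is indeed reasonable after surgery. But the article does not leave adherence to a later document: it states a rule as fixed in advance, and nothing in it excludes T1.

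Third, stopping may be rare. Staff visit daily, detached pellets are replaced, discharge ends the requirement, and the typical stay after breast-conserving surgery is 1 to 3 days. This is a fair reason to expect the lower end of the range; it does not mend the definition.

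Fourth, a reader might infer that some patients will receive pellets after the T1 questionnaire. The documents do not support that. The visible text leaves the order of application and T1 unclear, and Figure 1, which may show it, is not reproduced. What stands is that the rule itself does not require exposure before T1.

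Fifth, the selection is not confined to the NADA arm by construction, since controls who receive acupressure before Tx are also removed. It is still likely to be unequal: controls are offered acupressure only after their last measurement on the day of discharge, whereas NADA participants have several routes to stopping.

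**Conclusion.** The point holds as a fault in a stated definition. Applied to T1 outcomes, the continuation clause conditions on behaviour mostly later than the outcome, and the receipt clause is tied to the wrong event. Both affect only the exploratory per-protocol analysis.

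Two stronger readings should be resisted. One is that the trial's main result is compromised; it is not, because the intention-to-treat analysis ignores adherence. The other is that the rule flatters the intervention; the article gives no information on who stops or why, so the direction is unknown.

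Under the assumed 10-30% stopping and a 3-5 point gap between excluded and retained participants, the raw shift is 0.3 to 1.5 points either way, or 3.75% to 18.75% of the 8-point target. It is about 0 if later adherence is unrelated to the T1 score. These figures show a possible scale and are not a prediction.

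**What to change.** Use two adherence definitions.

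- **T1 outcomes (state anxiety and pain before surgery):** a NADA participant is adherent if the pellets were in place before the T1 assessment, and a control if she had no acupressure before T1.
- **T2-Tx outcomes:** keep the present 4-day-or-discharge rule and the present control rule.

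State also how the time of application relates to T1. The planned ANCOVA already adjusts for the baseline score, so no T0 covariate need be added.

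The cost is two sentences in the analysis plan and a recorded time of pellet application. The time of T1 has to be captured anyway, because Data Analysis plans an exploratory model using the interval from T1 to surgery. With 8 of 66 participants recruited at submission and no interim analysis planned, the change can be made before any comparison of outcomes is seen.
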